## Abstract

**Background:**

The Multi-Omics for Mothers and Infants (MOMI) Consortium aims to define biological mechanisms associated with preterm birth, small for gestational age, preeclampsia, and stillbirth. Globally, the burden of adverse pregnancy outcomes (APOs) is highest in low- and middle-income countries (LMICs). The MOMI Consortium consists of six different LMIC sites established by The Alliance for Maternal and Newborn Health Improvement in Bangladesh, Pakistan, and Tanzania, the Global Alliance to Prevent Prematurity and Stillbirth in Bangladesh and Zambia, and the Interdisciplinary Group for Advanced Research on Birth Outcomes – DBT India Initiative. It also partners with five analytical partners and three bioinformatic teams.

**Methods:**

The combined MOMI cohort includes 24 321 pregnant women, a rich biorepository, and paired socioeconomic and clinical data. Considering the multifactorial aetiologies and molecular drivers of APOs, we applied an integrative multi-omics (genomics, metabolomics, proteomics, nutrient testing) approach to identify site-specific and cohort-wide signatures linked to distinct APOs.

**Conclusions:**

This protocol summarises the MOMI study design, sample and data collection methods, data harmonisation, and the various analytics platforms, and discusses potential outcomes for enhanced clinical care and novel diagnostic and therapeutic tools.

Pregnancy complications such as preeclampsia (PE) and adverse pregnancy outcomes (APOs) such as preterm birth (PTB), small for gestational age (SGA), and stillbirth (SB) pose a serious global health challenge and collectively contribute to high rates of maternal and infant mortality and morbidity. Close to 2 million stillbirths were reported in 2020 [1,2] while more than half (55.3%) of the 2.4 million neonatal deaths were associated with PTB and/or SGA [1,2]. While numerous studies have explored the biological mechanisms of APOs, small sample size, geographic limitations, and inconsistent study designs hinder the generalisability of the findings. For example, a recent review of 147 studies on 56 pregnancy and pre-pregnancy cohorts from 26 different countries demonstrated that most studies were conducted in high-income countries, while specimens were collected in only about half of the studies and at varying time points [3].

Comprehensive multi-cohort studies with harmonised clinical data and longitudinally collected biological specimens at time points standardised across sites and cohorts are required to address these challenges. The Multi-omics for Mothers and Infants (MOMI) Consortium was formed in response to this need. It brings together diverse pregnancy cohorts from low- and middle-income countries (LMICs) in Asia and Africa: the Alliance for Maternal and Newborn Health Improvement (AMANHI) from Pakistan, Bangladesh, Tanzania; the Global Alliance to Prevent Prematurity and Stillbirth (GAPPS) from Bangladesh and Zambia; and the Interdisciplinary Group for Advanced Research on Birth Outcomes – DBT India Initiative (GARBH-INi). This creates a unique resource of 24 321 pregnant women with well-phenotyped pregnancy outcomes and longitudinally collected biospecimens. The Consortium partnered with five analytics partners and three bioinformatics teams to analyse longitudinally collected specimens for genomics (Cincinnati Children’s Hospital, Ohio, USA), metabolomics (Sapient Bio, California, USA), proteomics (Max Planck Institute for Biochemistry, Martinsried, Germany), and nutrient testing (UC Davis, California, USA, and International Centre for Diarrhoeal Disease Research (icddr,b), Dhaka, Bangladesh). The vast dataset of the various multi-omics and nutrient analyses, in combination with the sociodemographic and clinical metadata, will enable the MOMI Consortium to identify causal pathways through data integration and validate predictive biomarkers to develop clinically relevant interventions for mitigating APOs.

Only a few other studies of similar scope and magnitude have been performed or are ongoing. Analogous to the MOMI study design, a prospective study in China follows approximately 20 000 women in rural and urban centres to document maternal pregnancy outcomes and infant health [4]. The aforementioned Chinese study also aims to establish a large biorepository that will be utilised to define mechanisms associated with adverse outcomes among mothers and children by applying various omics platforms. The potential usefulness of such a multi-omics approaches in identifying biological pathways promoting APOs has been highlighted in a review about PE [5,6]. There are several other large-scale country-specific initiatives, such as the ORIGNS pregnancy and birth cohort in Western Australia [7], or the All of US Pregnancy cohort and the Nulliparous Pregnancy outcomes Study: Monitoring Mothers-To-Be in the US [8,9]. Most of these studies have established large biorepositories and databanks that are now accessible to researchers. Examples include IMPROVed [10], a biobank to study PE utilising specimens from four different European countries, or the Collaborative Online Perinatal and Pediatric Repository [11]. Precedence for the potential success of the international MOMI Consortium has been provided by other large global networks, such as the Intergrowth 21st project and its extension, the INTERBIO-21st project. The Intergrowth 21st project was an international collaborative consortium to establish international standards for foetal growth and to determine the association between gestational weight gain and APOs. The INTERBIO-21 is an extension of the Intergrowth 21 project that intends to define the impact of APOs on infant morbidity up to two years of age [6,12-14]. Akin to the Intergrowth 21st Network, the MOMI Consortium represents an international collaboration of clinicians and researchers in LMICs that were specifically chosen for their high incidence of APOs.

We hypothesise that the integration of data from multiple omics technologies will provide the means to define biological pathways that are altered in pregnant women with APOs and that, despite some overlap, unique signatures for PTB, PE, stillbirth, and SGA can be deduced to develop novel risk assessment tools and interventions. The inherent heterogeneity across the cohorts in different geographical locations will be counterbalanced by the tightly coordinated study design, data harmonisation, and adjudication of birth outcomes, and the extensively validated computational pipeline developed in prior studies [15-21]. Furthermore, only APO signatures that are reproducible across different cohort sites will be considered biologically and clinically meaningful. This protocol presents the objectives, study design, and analytical approaches of the MOMI Consortium and outlines how integration of multi-omics and metadata will enhance the understanding of pregnancy biology, inform risk prediction models, and contribute to the development of targeted interventions to improve maternal and infant health.

## STUDY DESIGN AND CONSORTIUM STRUCTURE

### Goals and governance

The MOMI Consortium (**Figure 1**) was established in 2018 to leverage large pregnancy cohorts in representative Asian and African LMICs with high risk for adverse pregnancy outcomes. Applying a set of distinct omics technologies to longitudinally collected specimen from women with term birth versus women with adverse pregnancy outcomes combined with coordinated data analysis and integration at each site and across sites was key to achieving the MOMI goals (**Figure 2**). The Consortium agreement provides a structured ethical framework, outlining data sharing, intellectual property rights, and authorship policies to ensure equitable contributions from all partners and emphasising fair collaboration between Global North and South institutions (Figure S1 in the **Online Supplementary Document**).

**Study visits**						
Enrollment	<24 weeks GA*	<20 weeks GA	<20 weeks GA			<20 weeks GA
Post enrollment, during pregnancy						10–14 weeks GA
	22–24 weeks GA		24–28 weeks GA			18–20 weeks GA
	26–28 weeks GA					26–28 weeks GA
	32 weeks GA		32–36 weeks GA			30–32 weeks GA
	36 weeks GA		Post-37 weeks GA			No
Delivery	Yes		Yes			Yes
Post-delivery	Week 6		1–6 days and infant at 42–60 days			Six weeks to six months
**Maternal specimens**						
Urine	Yes	Yes	Yes	Yes	Yes	Yes
Serum	Yes	Yes	Yes	Yes	Yes	Yes
Plasma	Yes	Yes	Yes	Yes	Yes	Yes
Blood	Buffy coat, whole blood	Whole blood	Buffy coat, DBS	Buffy coat	Buffy coat	DNA of whole blood
Placenta tissue	RNAlater, formalin, snap frozen		RNAlater, formalin, snap frozen			Formalin, snap frozen
Placenta membrane	RNAlater, formalin, snap frozen		RNAlater, formalin, snap frozen	No	RNAlater, formalin, snap frozen	RNAlater, formalin, snap frozen
Faecal sample (delivery)	Yes	No	Yes	Yes	No	No
**Infant specimens**						
Blood	Cord blood, DBS	Cord blood	DBS (72 hours)	Cord blood buffy coat	Cord blood	DNA of cord blood
Faecal Sample	Yes (delivery)	No	Yes (42–60 days)	Yes (42–60 days)	Yes (42–60 days)	No
						

AMANHI – Alliance for Maternal and Newborn Health Improvement, GAPPS – Global Alliance to Prevent Prematurity and Stillbirth, GARBH-INI – Interdisciplinary Group for Advanced Research on Birth Outcomes – DBT India Initiative, DBS – dried blood spots, GA – gestational age, PreSSMat – Preterm and Stillbirth Study, Matlab, ZAPPS – Zambian Preterm Birth Prevention Study

*Women living without HIV: 20 weeks of GA; women living with HIV: <24 weeks of GA.

### Sociodemographic and clinical data

Sociodemographic data (age, partner status, education, tobacco, alcohol and drug use), weight, medical history, parity status and, in case of prior pregnancy, pregnancy history and outcome, were documented at enrolment. A medical exam was conducted at the same time point that included body mass index, blood pressure (BP), and haemoglobin measurement, urine analysis, testing for HIV and other sexually transmitted diseases, assessment of pregnancy symptoms, and a dating ultrasound. Subsequent antenatal visits included determination of GA, recording of pregnancy symptoms since the prior visit, and testing for urine, haemoglobin, BP, heart rate, and weight. At delivery, medical conditions or medications during pregnancy and/or delivery, time of membrane rupture, delivery time, and birth outcome were documented. The foetus’s heart rate and fundal height were also assessed. Data also captured indications for provider-initiated delivery or caesarean section, postpartum complications, neonatal vital status, and Apgar score. Women and infants were seen at least once between six weeks to six months post-delivery. The infant was evaluated for any diseases and medications since birth, and evaluated for infant weight, head circumference, mid-upper arm circumference, temperature, heart and respiratory rates. The mother underwent a pelvic exam and was assessed for weight, BP, heart rate, temperature, and oedema.

### Study design

The MOMI Consortium progressed through three phases. The pre-pilot phase focused on sample quality assessment. The pilot phase was dedicated to the development and validation of the analytical workflows, while simultaneously harmonising the MOMI dataset, study outcomes, and analytical approaches [16,17,19,23,24]. The current phase (**Figure 3**) implemented population-scale molecular profiling of relevant specimens and continues with ongoing site-specific and cohort-wide data analysis and integration. Analyses are being performed on specimens collected during early (enrolment at <20 or <24 weeks GA), mid (22–28 weeks GA), and late pregnancy (28–36 weeks GA). These time points were selected to determine the dynamic trajectory of analytical factors throughout pregnancy, and test whether specific molecular signatures at one or multiple time points can predict the risk for specific APOs. Clinically, the earlier a risk for a specific APO can be identified, the higher the potential for adequate surveillance, improved clinical care, and prevention or reduced severity of the APO. Among the omics-platforms applied, metabolomics and proteomics will be applied to all longitudinal maternal specimens and cord blood, while the genomics analysis requires only a single sample from mother and infant. Maternal GARBH-INi specimens will also undergo genomics analysis. A sub-cohort study will include the longitudinal specimens of women with the most common APOs (PTB and SGA) and rare APOs (SB, very PTB, PE) plus a random sample from the full cohort (n = 5000) and 1000 women from the GARBH-INi cohort. These specimens are being analysed for nutrients group I, while in the GARBH-INi cohort, they are also being investigated for common bioanalytes and for proteomic and metabolomic APO signatures identified in the MOMI cohort. A nested case-control study (1:3) of the sub-cohort will consist of all specimens from women with rare APOs compared to women with term birth to test for biomarkers of epigenomics, nutrients of group II, and common bioanalytes. The common bioanalytes were selected based on their association with specific APOs and will only be measured at time points relevant to their role in pregnancy. Specifically, thyroid-stimulating hormone and pregnancy-associated plasma protein A will be tested in early pregnancy, whereas soluble fms-like tyrosine kinase and placental growth factor will be tested at mid and late pregnancy [25-31]. Placental tissues from a subset of women with PTB or term birth will undergo histopathology, transcriptomic, epigenomic, and global proteomic analysis.

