
### Statistical considerations

The case-cohort design was selected to balance statistical power, feasibility, and cost in a large, globally distributed pregnancy cohort. Full multi-omic profiling of all participants is neither economically nor logistically feasible, particularly for low-prevalence outcomes such as stillbirth and PE. The case-cohort framework enables comprehensive inclusion of all cases for each adverse pregnancy outcome while sampling a representative sub-cohort from the full population. This preserves the ability to estimate population-level risks and outcome prevalence, while substantially reducing assay volume and cost. This design also supports both outcome-specific analyses and integrative cross-outcome comparisons through the use of a shared reference sub-cohort. It retains the inferential strengths of a prospective cohort, while enabling deep molecular characterisation of rare and clinically important phenotypes. When integrating molecular and clinical data into cohort-level analyses, we will apply established case-cohort weighting and variance estimation methods (*e.g.* Prentice-weighted Cox models and survey-weighted regression frameworks) to ensure unbiased population-level inference and correct standard errors.

Nested case-control sampling is used for targeted assays and discovery-oriented analyses where relative contrasts between cases and matched controls are most informative and cost-efficient. These analyses will be interpreted as conditional, outcome-specific comparisons and will not be pooled directly with population-level estimates derived from the case-cohort framework. Where results from nested case-control analyses inform broader models, they will be re-estimated within the weighted case-cohort structure to preserve representativeness and avoid selection bias.

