### Statistical power

For high-dimensional, regularised machine-learning models operating across multiple molecular modalities, classical closed-form power calculations are not available. Instead, effective power is governed by the number of outcome events, feature dimensionality, and the cross-validation and regularisation strategy. The MOMI substantially exceeds the scale of prior pregnancy multi-omics studies, including those that have successfully identified reproducible molecular signatures of PE and PTB [17,19,20]. The inclusion of all cases for each adverse outcome, coupled with a large, representative sub-cohort, maximises event density and information content, while maintaining cohort-level validity.

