Due to the high cost-per-sample and medium/low sample throughput, a case-cohort study design categorised into the sub-cohort and nested case control study (**Figure 3**) was selected. The sub-cohort includes the longitudinal samples of approximately 30% of pregnant women in the full cohort and available cord blood samples for group I nutrient analysis (Figure S8 in the **Online Supplementary Document**). Nutrients of this group include vitamin A, D, E, folate, B12, total homocysteine, ferritin, transferrin receptor, iodine, minerals (copper, selenium, magnesium, calcium, phosphorus, iron, potassium, sodium), alpha-1-acid-glycoprotein, C-reactive protein, high-density lipoprotein, low-density lipoprotein, and triglycerides. It is noteworthy that the Group I Nutrient analyses will be performed by the icddr,b, representing the only in-country analysis. Group II nutrients (vitamins B1, B2, B3, B5, B6, B7, choline, and a targeted metabolomics panel) will be analysed in the longitudinal samples of PE, SB, and vPTB cases and their matched term controls (1:3 ratio). The B vitamins, choline and related metabolites will be measured by ultra-high performance liquid chromatography (UHPLC)- MS/MS and fatty acids and amino acids by UHPLC-MS/MS – MxP®Quant 500 XL kit [51,54].

As specimens of the GARBH-INi cohort will be analysed by the Translational Health Science and Technology Institute, India (THSTI), a harmonisation plan between THSTI and icddr,b, or between THSTI and UC Davis for nutrient group I or group II analyses, respectively, was developed. Institutions will apply standardised test methods, instrument calibration, quality control measures, external quality assurance schemes, and reporting methods. The joint analysis of the nutrient group I and II parameters from the GAPPS, AMANHI and GARBH-INi sites will allow for validation across sites and analytical platforms.

The placenta tissue analysis will be particularly valuable towards the goal of designing novel diagnostics or intervention strategies to prevent APOs, as several of the APOs are either entirely or partially attributable to placental dysfunction. These include early-onset PE, foetal growth restriction, and a subset of PTB cases. Since the placenta is in direct contact with maternal blood, placental APO signatures will likely be highly complementary to APO signatures in maternal blood and provide crucial information on the involvement of certain biological pathways.

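### As worded, the nested 1:3 term controls come from an outcome-enriched sub-cohort, which can roughly double the share of SGA women among them; draw them from the random part or weight them

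*Protocol article*

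**What the plan says.** The places below are all in the protocol article.

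- **Study design** composes the sub-cohort of "women with the most common APOs (PTB and SGA) and rare APOs (SB, very PTB, PE) plus a random sample from the full cohort". The sizes are given as "plus a random sample from the full cohort (n = 5000) and 1000 women from the GARBH-INi cohort".
- The same section then nests the second study in it: "A nested case-control study (1:3) of the sub-cohort will consist of all specimens from women with rare APOs compared to women with term birth". Epigenomics, group II nutrients and common bioanalytes are assigned to this nested study.
- **Analytical studies** (nutrient paragraphs) repeats the allocation as "PE, SB, and vPTB cases and their matched term controls (1:3 ratio" and sizes the parent set: "The sub-cohort includes the longitudinal samples of approximately 30% of pregnant women in the full cohort". Matching factors are not named, and SGA status is not mentioned.
- **Statistical considerations** says that all cases of each outcome are included while "sampling a representative sub-cohort from the full population", and makes the sub-cohort the shared reference. **Statistical power** says the cases are "coupled with a large, representative sub-cohort".
- Statistical considerations also says that nested results are read as conditional comparisons. They are re-estimated under case-cohort weights where they feed wider models.
- **Discussion** describes the comparison group as term, live-born and of appropriate weight, which would exclude SGA.

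**The concern.** SGA is itself one of the outcomes for which women enter the sub-cohort. On the Study design wording, a term SGA woman is in the control frame because she was selected as a case. A term woman without an APO is there only if the random draw picked her. SGA women can properly serve as controls for preeclampsia, stillbirth or very preterm birth at their natural frequency, but this frame multiplies that frequency.

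The consequence falls on the direct nested contrasts. For a marker that moves the same way in SGA and in the rare outcome, SGA-rich controls sit closer to the cases and the contrast shrinks. For a marker related only to SGA, a difference can appear that has nothing to do with the rare outcome. Matching on other factors leaves SGA over-sampled within the matched sets, and calling the comparison conditional does not change who the controls are.

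**Working it through.** **Inputs** (Table 2, combined MOMI cohort without GARBH-INi): N = 16 221; preterm birth 1587; stillbirth 168; SGA below the 10th percentile 3527; preeclampsia 290; very preterm 148. Random sample 5000 (Study design). The overlap of SGA with preterm birth and stillbirth is not given, so the full range is used.

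**1. The article's own figure.** f = 5000/16 221 = 30.8%, which reproduces the stated figure of about 30%. It does so if 5000 is the random sample alone, or if it is the whole sub-cohort. All cases plus 5000 random women would be larger: about 8050 to 8850 women, 50-55% of the cohort (0-50% overlap). So the 30% figure conflicts with the composition in Study design.

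**2. Which frame does the nested study need?** It is to be part of the sub-cohort and to hold all rare-APO specimens. Rare-APO entries number at most 148 + 290 + 168 = 606. A purely random 30.8% sample would be expected to hold about 0.308 × 606 = 187 of them. The enriched composition is therefore the natural reading of that sentence.

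**3. SGA share among term women.** Preterm birth is defined on live births, so term live births are at most T = 16 221 − 1587 − 168 = 14 466. Let S be the number of term SGA women. The cohort share is S/T. The share in the enriched frame is S/(S + f(T − S)).

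| Overlap assumed | S | Cohort share | Frame share | Ratio |
|---|---|---|---|---|
| None | 3527 | 24.4% | 3527/(3527 + 0.3082 × 10 939) = 51.1% | 2.10 |
| Independent (21.74% of 1755 = 382) | 3145 | 21.7% | 3145/(3145 + 0.3082 × 11 321) = 47.4% | 2.18 |
| Complete (all 1755 are SGA) | 1772 | 12.2% | 1772/(1772 + 0.3082 × 12 694) = 31.2% | 2.54 |

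The ratio of selection probabilities is 1/f = 3.24. By site, under independence and the same f, the ratio in share runs from 1.82 (AMANHI Bangladesh) to 2.67 (Tanzania).

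**4. What this does to a contrast.** Assume a marker shifted by d SD in SGA women. Under independence the control mean moves by (0.474 − 0.217) × d = 0.257d, which is 0.05 SD at d = 0.2 and 0.13 SD at d = 0.5. For a marker related only to SGA, the spurious case-minus-control difference is d × (SGA share in cases − SGA share in controls). With d = 0.5:

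| SGA share in cases (assumed) | Enriched controls | Natural-frequency controls |
|---|---|---|
| 21.7% | −0.13 SD | 0 |
| 40% | −0.04 SD | +0.09 SD |
| 47.4% | 0 | +0.13 SD |

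The two frames are equally far off at (47.4 + 21.7)/2 = 34.6%. The sign and size therefore turn on a share that the article does not report.

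**5. Is a random-only control set large enough?** Term women in the random part: 0.3082 × 14 466 = 4459. Controls needed: at most 3 × 606 = 1818. The tightest site is Zambia, where cases number at most 45 + 85 + 62 = 192. That needs 576 controls, against 0.3082 × (2576 − 223 − 62) = 706 term women if the random sample is proportional by site.

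**The case against.** The strongest reply is that no sentence says controls come from the APO-selected part. Statistical considerations and Statistical power treat the cases and a representative sub-cohort as two components. The 30% figure fits a random sample of 5000 alone. The group I count of more than 9500 samples points the same way: at 30 000/16 221 = 1.85 samples per woman it implies about 5140 women, not 8000 or more. On that reading the ratio is 1.0. If the Discussion's reference group governs, no control is SGA at all. Study design also does not say that all preterm and SGA women are included; that comes from the two statistical sections.

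This stands as far as it shows that the article supports more than one control frame, so bias cannot be asserted as fact. It does not remove the point. The one section that specifies the nested sampling gives the enriched frame, and a random 31% could not hold every rare-APO woman.

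The second reply is the promised re-estimation. It is a real safeguard but a partial one. It applies only where nested results feed wider models, and the direct nested contrasts are not said to be weighted.

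Two stronger readings are tempting and should not be drawn:

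- **A four-fold excess.** This requires 5000 to be the whole sub-cohort with every case inside. The text attaches 5000 to the random sample. Without overlap the cases alone, 3527 + 1587 + 168 = 5282, would already exceed 5000.
- **A false-positive rate of 28-50% for SGA-only markers.** This assumes d = 0.5, 290 preeclampsia cases against 870 unmatched controls, nominal p < 0.05, and cases with the cohort's SGA share. Data harmonisation counts growth restriction or birth weight below the 3rd percentile as preeclampsia evidence, so that share is probably higher among cases. The analysis section specifies false discovery rate control. The rate is at most a conditional illustration.

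**Conclusion.** The concern holds in a conditional form. As Study design is worded, the nested controls are term births from an outcome-enriched sub-cohort. If all SGA cases are in it, 5000 is the random part and sampling is unweighted, SGA is over-represented among term controls about 2.1- to 2.5-fold across the whole range of possible overlap (21.7% to 47.4% under independence). The direct rare-APO contrasts for SGA-related markers can then be biased, in a direction and by an amount that the article's figures cannot settle. A reader might infer that the contrasts are certainly distorted or that nothing in the plan addresses it; the documents support neither. The descriptions of the reference group (enriched set, representative sample, about 30% of the cohort, term births of appropriate weight) do not agree and need to be reconciled.

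**What to change.** 1. In Study design and in the group II nutrient paragraph, state that nested term controls are drawn only from the random-sample part of the sub-cohort. This returns the SGA share to the cohort value. It costs a wording change and one change to the control-selection program.
2. If controls are already drawn or assayed, weight each by the inverse of her probability of being in the sub-cohort: 1 for women selected for an APO, 1/0.308 = 3.24 for women present only through the random draw. Selection into matched sets has to be carried through as well. With 47.4% of controls at weight 1 and 52.6% at 3.24, the effective control number is (0.474 + 0.526 × 3.24)²/(0.474 + 0.526 × 3.24²) = 79% of the actual number, a moderate loss of precision.
3. In Statistical considerations and Statistical power, reserve the representative sub-cohort and the shared reference for the random part.
4. Reconcile the control definition with the Discussion by saying whether term SGA women are eligible. If they are not, check supply by site. In Zambia about 706 × (1 − 0.168) = 587 term women would remain for up to 576 controls, before any with preeclampsia are removed.
5. State whether 5000 and 30% describe the random part or the whole sub-cohort.
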